#### Secondary mechanism of change measures

##### Pro-inflammatory cytokines

To examine inflammation, participants will collect a morning (1 h after habitual wake time) and evening (12 h after first sample collection) salivary sample to assay for interleukin-1 and -6.

##### Continuous glucose monitoring

Continuous glucose monitoring will be conducted to examine daily patterns of glucose activity and their amplitude. Continuous glucose monitoring will be performed using the Dexcom, G6 CGM. Researchers will place the CGM onto the back of the upper arm of participants to ensure proper placement which will also activate the CGM. Participants will not have access to data while wearing the monitor. Participants will wear the G6 CGM monitor for 10 days at both baseline and week 6, before removing the sensor using instructions provided.

##### Comprehensive metabolic screen and glucose tolerance test

A broad metabolic screen and glucose tolerance test will be conducted by Quest Diagnostics in a single visit to measure metabolic health parameters at both baseline and week 8. Participants will log into a Quest Diagnostics portal specific to this study to schedule the appointment.

#### Intervention acceptability probes

We will use acceptability probes previously validated in the ORBIT clinical trial for BD [98], rated on a scale from “Strongly Disagree” to “Strongly Agree”. Ratings of “agree” or “strongly agree” for each item will be considered acceptable. Our primary index of acceptability will be the percentage of individuals who endorse that they agree or strongly agree that they would recommend the food plan to a friend, but we will share responses on each item for transparency.

We will supplement these probes with questions to assess whether individuals perceive that their mania, depression, sleep, or quality of life improved or worsened with TRE. As a further check of potential negative outcomes, participants will be asked open-ended queries regarding problems associated with TRE.

#### TRE adherence

We will score adherence using well-validated metrics to evaluate the time of first and last caloric intake each day. To reduce skew from infrequent deviations from the eating plan, we will define the time interval that contains 95% of intake events [127]. Consistent with other US and European studies of TRE, we will define adequate logging for a given day as entry of at least two intake events covering at least a 5-h window. Focusing on the days with adequate logs, we will calculate the percentage of the days in which individuals met the eating window goal. High adherence will be defined as meeting this standard on at least 78% of the days with adequate logs. As supplemental data, we will report the percentage of days logged and the percentage of days in which individuals logged adequately and followed the planned window.

#### Potential moderators

We will gather several variables to assess their role in moderating outcomes. These include data on the types of psychotropic and sleep medicines, doses, and adherence levels at each self-report assessment to calculate summary scores for each major receptor type. At baseline, we will gather data on the Positive Urgency Scale [128], food insecurity (HFSSM; [94, 129]), and Menopause QoL sleep items [96, 97], as potential predictors of intervention outcome. At baseline and at 6 weeks, we will gather a Food Frequency Questionnaire to assess inadvertent changes in dietary intake (e.g., less dessert consumption after participants stop midnight snacks).

### Reasons for discontinuation from study

To support intent-to-treat analyses, we will attempt to gather final outcome assessments for all participants who discontinue the study (except those who explicitly discontinued or were withdrawn on ethical grounds. This final outcome assessment will include an intervention acceptability survey, self-rated mania, depression, and QoL; and, if participants are willing, the YMRS, MADRS, and the LIFE. The trial coordinator will attempt to contact participants who withdraw by phone to ask the main reasons for discontinuation. Should adverse events be discovered, those will be reported.

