**Methods:**

One-hundred fifty participants diagnosed with BD 1 or II will be recruited via advertising in the local community. Main inclusion criteria include: obtaining medical treatment for BD; current sleep or circadian problems; self-reported eating period of ≥ 12 h; no eating disorder or other health conditions that would hinder or limit the safety of following TRE; and not currently experiencing a mood episode, acute suicidality, psychosis, alcohol or substance use disorder. Participants will be asked to complete a baseline period in which daily food intake is logged online for two weeks. After baseline, participants will be asked to follow TRE for 8 weeks and to continue to complete daily food logging during this time. Symptom severity interviews will be conducted by phone or videoconference at baseline, mid-intervention (6 weeks post-baseline), end of intervention (10 weeks post-baseline), and 6 months post-baseline. Self-rated symptom severity and quality of life data will be gathered online at the same time points as symptom severity interviews, and at 16 weeks post-baseline (6 weeks after the TRE period ends). To assess potential mechanisms of change, we will examine the change in diurnal amplitude of ‘clock’ gene expression as a primary mediator at 8 weeks compared to baseline. We will further test whether diurnal amplitude of clock gene expression is predictive above and beyond the role of two covariate potential mediators, glucose tolerance and inflammation at 8 weeks relative to baseline. To provide an index of whether TRE successfully decreases emotional lability, participants will be asked to complete 5 mood assessments per day for 7 days at baseline and at 10 weeks. These mood assessments will be optional.

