##### Symptom, mood, and quality of life (QoL) assessments

Symptom severity and LIFE interview assessments will be conducted at the midpoint, at the end of the 8-week TRE period (week 10) and at 6 months after the end of baseline. Self-rated assessments of symptom severity and sleep/circadian variables will be conducted at each of those assessments and at 16 weeks post baseline. The EDE-QS will be administered at midpoint and post intervention. Participants will be asked to complete EMA for 7 days post intervention. Secondary outcome measures will be assessed post intervention.

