#### Adverse events

In addition to the risk management procedures, we will take several steps to minimize the potential for adverse events. For participants who experience the onset of symptoms, we will consider with participants whether it would be helpful to take a break from the study if requirements might interfere with placing a focus on recovery. For participants who choose to take a break from the study, and interviewers will schedule a time to check in to consider restarting trial engagement. Techniques for routinely assessing adverse events, responding to signs of adverse events, and reporting such events are detailed elsewhere [69].

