**Fig. 1 Fig1:**
[figure not shown]
Assessment timing

**Table 1 Tab1:** Schedule of assessments

Measure	Format	Screening	Baseline	Mid-Intervention (Week 8)	Post-Intervention (Week 10)	Week 16 Follow Up	6 Month Follow Up

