***Screening Self-Report***							
DIAMOND Self Report Screener Psychosis Subscale	SR	X					
Alcohol Use Disorders Identification Test (AUDIT)	SR	X					
Drug Use Disorders Identification Test (DUDIT)	SR	X					
Short Eating Disorder Examination Questionnaire (EDE-QS)	SR	X		X	X		
Insomnia Severity Index (ISI)	SR	X					
Munich ChronoType Questionnaire (MCTQ)	SR	X					
Brief Social Rhythms Scale (BSRS)	SR	X					

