***Screening Interview***							
Orientation, Memory and Concentration Test (OMC)	I	X					
Diagnostic Interview for Anxiety, Mood, and OCD and Related Neuropsychiatric Disorders (DIAMOND)	I	X					
Columbia Suicide Severity Rating Scale (C-SSRS)	I	X					
Structured Clinical Interview for Sleep Disorders—Revised (SCISD-R)	I	X					

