##### Short Eating Disorder Examination Questionnaire (EDE-QS; [83])

The EDE-Q short form is a 12-item self-report measure designed to assess a range of eating-related symptoms, including restraint, eating concern, shape concern and weight concern [109]. The EDE-QS has shown strong internal consistency (Cronbach’s α = .913, high temporal stability (ICC = .93), and high correlations with eating disorder diagnoses and original EDE-Q scores (r’s > 0.81).

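### Minor, cheap improvement: the exit assessment omits the EDE-QS, so anyone who leaves before the mid-intervention visit has no eating-disorder score after entry

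*Protocol article*

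**What the plan says.** The section on reasons for discontinuation gives the exit assessment a purpose, supporting intention-to-treat analyses, and a content. It reads "This final outcome assessment will include an intervention acceptability survey, self-rated mania, depression, and QoL", and adds the YMRS, MADRS and LIFE for participants who agree to them. It exempts people who explicitly discontinued or who were withdrawn for ethical reasons. It also plans a telephone call to ask why a participant left, and reporting of any adverse event that comes to light.

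The section on symptom, mood and quality of life assessments states that "The EDE-QS will be administered at midpoint and post intervention". Table 1 agrees: the row "Short Eating Disorder Examination Questionnaire (EDE-QS") is marked at screening, mid-intervention and post-intervention only. The other instrument that covers eating disorders, the "Diagnostic Interview for Anxiety, Mood, and OCD and Related Neuropsychiatric Disorders (DIAMOND"), is marked at screening only.

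The midpoint has two dates. The abstract gives "mid-intervention (6 weeks post-baseline), end of intervention (10 weeks post-baseline"), while the Table 1 column is headed "Mid-Intervention (Week 8").

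**The concern.** The intervention restricts the hours of eating in a psychiatric population, and the plan treats eating disorder as a risk at entry. It excludes on self-reported history, on an EDE-QS score of 15 or more, and on a DIAMOND diagnosis. The EDE-QS is then repeated during and after TRE, so it is the one structured measure on which a participant's later state can be compared with the state at entry.

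Those comparisons exist only for people who reach the midpoint. Someone may leave because eating symptoms have appeared or worsened, so whether a score is missing may depend on the symptom being scored. Scores from those who remain could then understate harm, and in a single-arm study there is no control group against which to notice it. A score that is not taken at exit cannot be recovered later by any analysis plan, which is why the exit list is the place to raise this.

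**Working it through.** The plan states no figure on this point to reproduce. The check is a count of measures and a comparison of dates.

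**1. Exit measures listed (Reasons for discontinuation from study)**
- Self-report: acceptability survey, self-rated mania, self-rated depression, quality of life = 4.
- Interviews, if the participant is willing: YMRS, MADRS, LIFE = 3.
- Total: 4 + 3 = 7. EDE-QS among them: 0.

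**2. Eating-disorder instruments by time point (Table 1)**

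| Instrument | Screening | Baseline | Mid | Post | Week 16 | 6 months |
|---|---|---|---|---|---|---|
| EDE-QS | X | | X | X | | |
| DIAMOND | X | | | | | |

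Only the EDE-QS is repeated after entry.

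**3. Period without a score after entry**
- TRE lasts 8 weeks and ends at week 10, so it starts at week 10 − 8 = 2, directly after the two-week baseline.
- Midpoint at week 6 (abstract): 6 − 2 = 4 weeks into TRE; 4/8 = 50%.
- Midpoint at week 8 (Table 1): 8 − 2 = 6 weeks into TRE; 6/8 = 75%.

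**4. Scheduled EDE-QS scores after entry, by time of leaving**
- Leaves before the midpoint: 0.
- Leaves between the midpoint and post-intervention: at most 1.
- Completes: 2.

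**5. How many people**
- The analysis plan section allows for 25 of 150 participants being lost (25/150 = 16.7%). It does not say how many would leave before the midpoint, or why. Within that allowance the number could be anywhere from 0 to 25. No rate is assumed here.
- The 50% and 75% are shares of the TRE period. They are not shares of people, and they do not measure bias.

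**The case against.** The strongest reply is that the exit list suits its declared purpose. It is there to support intention-to-treat analyses; it covers all three primary outcomes; and the EDE-QS is neither an outcome nor part of any hypothesis. Table 1 files it under screening. The article plans no EDE-QS rate and states no action threshold during TRE, so no planned analysis is biased. All of that stands, and it is why the point is minor. The same section nevertheless also collects acceptability, reasons for leaving and adverse events, so it already serves more than the efficacy model.

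A second reply is that eating problems can surface in other ways: the withdrawal call, the open-ended questions on problems with TRE, optional coaching, and adverse-event procedures, for which the article says that techniques for "reporting such events are detailed elsewhere". This also stands, and the source it points to was not available for this check. The point is therefore limited to the missing scale score; it does not claim that such problems would go undetected. None of these routes, as described in the article, gives a score comparable with entry or with the cut-off of 15.

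Third, the exit list may not be exhaustive, and a fuller protocol may add the scale. That is possible, but the list is detailed enough to separate core from optional measures, and if the scale is already collected, naming it settles the matter.

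Lastly, some leavers are exempt from the exit assessment, so the added form would not reach everyone. That is correct, and it is the reason for also reporting a count.

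**Conclusion.** The point holds as a minor, optional improvement to data collection. As the article stands, people who leave the study during the first 4 of 8 TRE weeks (week-6 midpoint) or the first 6 of 8 (week-8 midpoint) have no eating-disorder score after entry, and later leavers have one at most. The number affected and the size of any distortion are unknown. No primary hypothesis, stated figure or planned EDE-QS analysis is affected.

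The conclusion rests on reading the exit list as complete and on week numbers that run from the start of the two-week baseline. The gap exists under either date for the midpoint. People who stop TRE but stay in assessment are outside this point, since they keep the scheduled EDE-QS visits.

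**What to change.** For anyone who has started TRE, add the EDE-QS to the self-report part of the exit assessment, making five self-report measures instead of four. Wherever EDE-QS results are reported, state how many participants started TRE but have no score after entry, because the exempt leavers will not receive the form.

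The cost is one short form on an assessment that is already planned ("The EDE-Q short form is a 12-item self-report measure"), and one count in the report. The only drawback is slightly more burden at exit.

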### Statistical analysis plan

Before conducting analyses of hypotheses, we will examine whether values appear to be missing at random. If this missing value imputation assumption is supported, we will impute data using 20 resamples, using demographic (sex/gender, age), baseline symptom severity, and symptom history variables (number of episodes) to predict missing scores. For comparison, we will perform analyses without imputed values. Data cleaning will be completed as described above in data quality. Statistical analyses will be conducted in accordance with the International Conference on Harmonization E9 statistical principles.

Before conducting analyses of hypotheses, we will carefully examine potential confounds. We will avoid adding any covariates that were entangled with our core mechanisms (e.g., sleep and circadian processes). With this in mind, we will only consider covariates for inclusion in models if they could be confounding our main effects– that is, those that are significantly correlated with both our IV (treatment adherence) and DVs (symptoms and QoL). Power analyses were based on inclusion of two covariates, and we would hope not to exceed this number of covariates. If more than two potential covariates are identified that appear significantly and uniquely correlated with both the IV and DVs, we would redo our power analyses, but at this point, we would be able to consider the covariance matrices, allowing for more careful estimation of true statistical power. We would consider these issues without generating the models of how our treatment variables actually influence symptoms and QoL, so as to avoid p-hacking or “fishing”. Only if those power analyses suggested that we could include more than 2 variables as confounds would we proceed to add more covariates; otherwise, we would plan to choose the two covariates that appear to hold the highest unique correlations with IV and DVs.

Analyses will be conducted using two-tailed tests with alpha set to .05.

Our core hypotheses will be tested using two parallel structural equation models (SEM) to consider mania and depression separately. In each, we will examine paths from TRE adherence levels to a latent variable for clock gene amplitude (based on 3 genes) to symptoms to QoL, controlling expected covariates and evaluating the potential confound of glucose tolerance mediation.

We have planned analyses based on availability of data from 125 participants, allowing for attrition of 25 participants. We assume moderate effects for diurnal amplitude on symptoms and QoL (f2 = .25) because smaller effects are inconsistent with the circadian rhythm theory. Assuming f2 = .40 (symptoms to QoL), power to detect the indirect effect of change in amplitude of gene expression on QoL via symptom change is .81, and for full model (RMSEA) > .90 [130, 131]. Intervention-related effects will be estimated using an intention-to-treat approach, in which we will examine final scores (where available) for all participants.

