#### Hypotheses

To examine the mechanisms through which TRE leads to symptom improvements, we will investigate a battery of biological measures at baseline and 8 weeks. We predict that TRE adherence will lead to a change in the amplitudes of diurnal clock gene expression and diurnal phase (DLMO) at 8 weeks, which will lead to a cascade of change in symptoms (mania and depression at week 10, and then a downstream change in QOL at 16 weeks).

H1: TRE adherence will predict changes in diurnal amplitude of clock gene expression from baseline to week 8.H2: The degree of change in diurnal amplitude of clock gene expression (at week 8) will be associated with the degree of improvement in symptoms (week 10), controlling for change in glucose tolerance and inflammation (week 8) and for baseline levels of diurnal amplitude, symptoms, glucose tolerance, and inflammation.H3: There will be an indirect effect of TRE adherence on QoL through symptoms.

Ambulatory data will provide opportunity for lagged tests of how biological rhythmicity improvements (actigraphy RA) promote improved sleep, resulting in diminished mood variability (ecological momentary assessment; EMA Mood Zoom) [74].

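### The stated imputation predictors leave out adherence, amplitude, follow-up symptoms and QoL, so the imputed analysis shrinks the H1–H3 paths that have an imputed end

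*Protocol article*

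**What the plan says.** All of this is in the Statistical analysis plan section of the protocol article unless noted.

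- **Condition for imputing.** Before testing hypotheses, "we will examine whether values appear to be missing at random. If this missing value imputation assumption is supported", imputation goes ahead.
- **Method.** "we will impute data using 20 resamples", "using demographic (sex/gender, age), baseline symptom severity, and symptom history variables (number of episodes) to predict missing scores". No other section adds predictors.
- **Comparison.** "For comparison, we will perform analyses without imputed values". The article does not say which analysis decides if the two differ.
- **Core analysis.** In two parallel SEMs, one for mania and one for depression, "we will examine paths from TRE adherence levels to a latent variable for clock gene amplitude (based on 3 genes) to symptoms to QoL". In the Hypotheses section, H2 is tested "controlling for change in glucose tolerance and inflammation (week 8) and for baseline levels of diurnal amplitude, symptoms, glucose tolerance, and inflammation".
- **Expected loss.** "We have planned analyses based on availability of data from 125 participants, allowing for attrition of 25 participants".

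**The concern.** An imputation model has to contain at least the variables and relations that the analysis will estimate. Here the analysis estimates adherence to amplitude, amplitude to symptoms, and symptoms to QoL. Of those variables and the H2 adjusters, the listed predictors contain only baseline symptoms. A missing amplitude drawn from age, sex/gender, baseline symptoms and number of episodes has no relation to that person's adherence or later symptoms beyond what baseline carries. Mixing such records with the observed ones dilutes the associations that the trial was set up to measure.

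The list also passes over good predictors that the study already collects. Table 1 schedules MADRS, YMRS, PHQ-9, PMQ-9 and QoL.BD repeatedly during and after the intervention.

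H1 to H3 are at stake. A diluted indirect effect could be read as evidence against the circadian mechanism when the imputation step caused part of the shortfall.

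**Working it through.** **The plan's own figure.** The article gives no figure for bias from imputation. Its related figure is a power of .81 for amplitude change to QoL through symptom change. With f² = .25 and .40 at N = 125, joint-significance power comes to .9998. Reading .25 and .40 as correlations gives .815. That mismatch is a separate matter, but because of it both readings are carried below.

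**Inputs from the article.** Missing fraction m = 25/150 = 1/6. Effects are .25 (amplitude to symptoms) and .40 (symptoms to QoL).
- Read as f², the standardised path is √(f²/(1+f²)): √(.25/1.25) = .447 and √(.40/1.40) = .535.
- Read as path coefficients, they are .25 and .40.

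**Assumptions, not in the article.**
- Adherence to amplitude (a) equals amplitude to symptoms (b).
- Baseline to follow-up symptoms is .40.
- Adherence and baseline symptoms are uncorrelated.
- The same 25 people lose amplitude, symptoms and QoL completely at random.
- Each missing score is drawn from the listed predictors only.
- Regressions on observed scores stand in for the latent SEM.

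Paths are shown as magnitudes.

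**Step 1: covariances after imputation.** Write X adherence, M amplitude, S symptoms, Q QoL, with c the symptoms-to-QoL path. In imputed records cov(X,M) = cov(M,S) = 0, and S and Q are linked only through baseline: .40 × .40c = .16c. Over all 150:
- cov(X,M) = (5/6)a = .833a
- cov(M,S) = (5/6)b = .833b
- cov(S,Q) = (5/6)c + (1/6)(.16c) = .86c

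**Step 2: simple chain, each path on its immediate predictor (plus baseline for symptoms).** The paths fall 17%, 17% and 14%. Amplitude–symptoms–QoL keeps .833 × .86 = .717, a fall of 28%. The three-path product keeps .833 × .717 = .597, a fall of 40%. These factors do not depend on the effect size.

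**Step 3: paths adjusted for the earlier variables (f² reading).**
- cov(X,S) = .833 × .447 × .447 = .167, and .373² = .139.
- b becomes (.373 − .373 × .167)/(1 − .139) = .361, a fall of 19%.
- Given baseline, var(S) = 1 − .16 = .84 and cov(S,Q) = .833 × .535 × .84 = .374. Also cov(M,Q) = .833 × .447 × .535 = .199.
- c becomes (.374 − .373 × .199)/(.84 − .139) = .428, a fall of 20%.
- The products are .361 × .428 = .155 against .239 (−35%), and .373 × .155 = .058 against .107 (−46%).

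**Step 4: simulation of the adjusted model** (N = 150, Rubin pooling; 20 imputations with the listed predictors, 10 with the SEM variables added).

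| Reading | Imputation | a | b | c | bc | abc |
|---|---|---|---|---|---|---|
| f² | true value | .447 | .447 | .535 | .239 | .107 |
| f² | listed predictors | .372 | .359 | .427 | .153 | .057 |
| f² | SEM variables added | .447 | .448 | .534 | .239 | .107 |
| coefficients | true value | .25 | .25 | .40 | .100 | .025 |
| coefficients | listed predictors | .208 | .209 | .328 | .068 | .014 |
| coefficients | SEM variables added | .249 | .254 | .399 | .101 | .025 |
| coefficients | none (unimputed) | .249 | .254 | .400 | .102 | .025 |

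In the f² reading the two products fall 36% and 47%, in line with Step 3. The quoted ranges therefore reflect two things: how .25 and .40 are read, and which other variables each path regression contains. Separate simulations of the simpler set-up gave 14–18% per path, 27–29% and about 40%.

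**Step 5: what is not attenuated (f² reading).** The baseline-symptom path stays at .40. If only amplitude is missing, symptoms to QoL stays at .542, its full-data value in those runs. If only symptoms and QoL are missing, adherence to amplitude stays at .448. Some direct paths that are truly zero move away from it: adherence to symptoms reaches −.076 when only amplitude is missing.

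**The case against.** **The list may not be exhaustive.** The article condenses a longer plan, and Data Availability mentions a statistical analysis plan that is not shown. If the named variables are only auxiliaries to a joint model of the SEM variables, the bias disappears. This stands as a caveat. But the article states the list without a qualifier such as 'including', and nothing in it points to a joint model.

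**The unimputed analysis is a safeguard.** It is unbiased when data are missing completely at random, so it would expose the attenuation. A reader might infer that the plan compares two flawed answers. Under this mechanism that is not so, and the wording does not even restrict that analysis to complete cases. What remains is that it is labelled a comparison and no rule says which result counts.

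**Stronger readings that the article does not support.**
- *Every SEM path shrinks, and imputed records carry no mediation signal.* Step 5 shows otherwise. Partly observed records keep the signal on their observed links.
- *Power collapses.* Under the f² reading, joint power stays near 1 with the planned attrition. Under the correlation reading it is about .71 with the listed predictors, against .82 with the SEM variables added and .85 unimputed. Larger losses need different people to lack different variables, which leaves more than the planned 25 incomplete.
- *The condition would switch imputation off where complete cases are most biased.* The article asks about missing at random. Missingness related to observed data is compatible with that, so this inference assumes a test that the text does not describe.

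**Follow-up of discontinuers.** The article plans final self-ratings for most people who stop, and interviews if they are willing. Loss of all three variables together is therefore a pessimistic pattern. With only amplitude missing (f² reading), amplitude–symptoms–QoL is .184 against .239, a fall of 23%.

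**Conclusion.** The point holds in a bounded form. Imputing from the list as written biases toward zero the hypothesised paths with an imputed end, and with them the indirect effects, even under the most benign missingness. With 25 of 150 losing amplitude, symptoms and QoL together, the falls are about 14–20% per path, 27–36% for amplitude–symptoms–QoL and 40–47% for the three-path product. These sizes rest on the assumptions under working, chiefly that the list is complete and that adherence to amplitude, which the article does not state, equals amplitude to symptoms.

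Making imputation conditional on "If this missing value imputation assumption is supported" is a lesser flaw. Observed data can show departures from missing completely at random but cannot confirm missing at random, so the check cannot do the job it is given.

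This should be fixed before analysis. It is not fatal, because the main bias is conservative, an unimputed analysis is planned, and no data are lost.

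**What to change.** Either of two changes is enough:

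1. Estimate the SEM by full-information maximum likelihood.
2. Keep the 20 imputations and the listed predictors, and add every SEM variable: adherence, baseline and week-8 amplitude, glucose tolerance, inflammation, symptoms and QoL. Use the repeated symptom and QoL scores, clinician-rated and self-rated, as auxiliaries.

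In both cases, drop the condition that missing at random must first be supported; state it as an assumption. Say in one sentence whether the imputed (or likelihood) analysis or the unimputed one decides H1 to H3. If the full plan already imputes the SEM variables jointly, a sentence saying so settles the main point.

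The cost is analysis wording and code. No new data, visits or participants are needed.

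### The listed imputation predictors omit the variables of the mediation model, so if followed as written they attenuate the hypothesised paths that involve imputed values

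*Protocol article*

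**What the plan says.** All of the following is in the Statistical analysis plan section of the protocol article unless noted.

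- Imputation is conditional on a check of the missingness mechanism: "If this missing value imputation assumption is supported, we will impute data using 20 resamples". The predictors are then named: "using demographic (sex/gender, age), baseline symptom severity, and symptom history variables (number of episodes) to predict missing scores".
- A second analysis is planned: "For comparison, we will perform analyses without imputed values". The text does not say which of the two is primary.
- The core model has "paths from TRE adherence levels to a latent variable for clock gene amplitude (based on 3 genes) to symptoms to QoL", fitted once for mania and once for depression, "controlling expected covariates and evaluating the potential confound of glucose tolerance mediation". H2 in the Hypotheses section also adjusts for change in inflammation and for baseline amplitude, symptoms, glucose tolerance and inflammation.
- The sample size rests on 125 of 150 participants, "allowing for attrition of 25 participants". The stated power for the amplitude–symptoms–QoL indirect effect is .81, with f2 = .25 and f2 = .40.
- The section on reasons for discontinuation plans a last assessment for most participants who leave. It covers self-rated symptoms and QoL, and the MADRS and YMRS only if the participant is willing.

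**The concern.** Multiple imputation preserves only the associations that the imputation model contains. The named predictors are demographics, baseline symptoms and episode history. Adherence, the gene amplitudes, glucose tolerance, inflammation, follow-up symptoms and QoL are all in the analysis model, but none is a named predictor. A value of amplitude, symptoms or QoL drawn from the named predictors alone is independent of these variables given baseline. Each imputed case therefore brings a null association into H1, H2 or H3, whichever of them uses the imputed variable.

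This is a single-arm mechanism study, and its core results are these path coefficients and their product. The attenuation needs no informative dropout. It arises under missing completely at random, so the planned check of the missingness assumption gives no protection.

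**Working it through.** **The plan's own figure.** The only related figure is the power of .81. With N = 125, two-sided alpha .05 and one tested degree of freedom, the noncentrality is f2 × N: .25 × 125 = 31.25 and .40 × 125 = 50. Joint significance of the two paths then has power above .99, and a Sobel version gives .99. Reading .25 and .40 as standardised paths gives .815, and reading them as f gives .787. So .81 does not follow from the stated f2 values. That is a separate matter, but it means that power must be shown under both readings. The documents give no figure for imputation bias.

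**Expected attenuation.** Let p be the fraction of cases in which a path has an imputed end. In the completed data the covariance is (1 − p) times its true value, because imputed pairs contribute about zero given baseline. The variance of the predictor is about unchanged. So slope ≈ (1 − p) × true slope, and a product of k affected paths ≈ (1 − p)^k.

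- p = 25/150 = 0.167
- One path: 1 − 0.167 = 0.833
- Two paths (amplitude–symptoms–QoL): 0.833² = 0.694
- Three paths (from adherence): 0.833³ = 0.579

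**Simulation.** N = 150, with 25 participants missing amplitude, symptoms and QoL together, completely at random; 20 imputations, Rubin's rules, 1,500 replicates. Standardised paths are √(.25/1.25) = .447 and √(.40/1.40) = .535. Three assumptions are not in the documents: adherence to amplitude is also set at .447, amplitude is a single observed variable, and one baseline variable stands in for the listed predictors. Entries are estimate divided by truth.

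| Analysis | Adherence→amplitude | Amplitude→symptoms | Symptoms→QoL | Two-path product | Three-path product |
|---|---|---|---|---|---|
| Listed predictors | 0.83 | 0.83 | 0.83 | 0.69 | 0.57 |
| All model variables | 1.00 | 1.00 | 1.00 | 1.00 | 1.00 |
| Without imputation | 1.01 | 1.01 | 0.99 | 1.00 | 1.02 |

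Further runs of this dropout pattern put the paths as low as 0.80 and the two-path product between about 0.65 and 0.72. With 15 missing (10%) the paths are at 0.90 and the two-path product at 0.81. With 37 missing (25%) they are at 0.75 and 0.56.

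**Other missingness patterns, 25 missing, listed predictors only.**

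- Amplitude alone missing (outcomes fully retrieved): adherence→amplitude 0.83, amplitude→symptoms 0.82, symptoms→QoL unaffected, two-path product 0.82.
- Outcomes retrieved for about half: two-path product 0.77.
- Symptoms alone missing: adherence→amplitude unchanged, amplitude→symptoms 0.84, symptoms→QoL 0.81. A direct adherence→QoL path (assumed true value 0.1) rises to 1.54 of truth.
- Glucose tolerance alone missing: amplitude→symptoms rises to 1.07 of truth, because adjustment is incomplete.
- Amplitude, symptoms and QoL missing together, glucose tolerance in the model (assumed coefficient 0.2): glucose→symptoms 0.99 and baseline symptoms→symptoms 1.00.

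**Power for the two-path effect, 25 missing together.** At the stated f2 values it is at or above .99 in all three analyses. With standardised paths of .25 and .40 it is .67 with the listed predictors, .79 with all model variables and .78 without imputation.

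**The case against.** Several replies have force.

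*The list may not be exhaustive.* The article does not say whether incomplete variables also predict one another, as they would under chained equations. If they do, and the same 25 people miss amplitude, symptoms and QoL, only adherence→amplitude stays attenuated (0.83). This stands as a limit on size. It does not rescue H1, and the text as written names a specific set.

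*Outcomes will be sought from those who leave.* This also stands: the loss in the indirect effect is then nearer 18% than 35%. But amplitude would still be missing, so the paths for H1 and H2 remain affected. The interview scores are retrieved only from those who are willing.

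*An analysis without imputed values is planned.* True, and under missing completely at random it does not share the bias. Its stated role as a comparison leans towards the imputed analysis as the main one, and a reader might infer that the imputed analysis is primary. The text never says so. What remains is that the two analyses could disagree because of the imputation model, and the disagreement could be put down to the missing data.

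Three other strong readings are tempting and not supported. One is that every path in the model shrinks; the patterns above show some unchanged and some inflated. Another is that the trial loses much of its power; at the stated f2 values it does not, and larger losses need path sizes that the documents do not give. The third is that adherence and mid-intervention scores will be on hand for many who drop out; no dropout timing is given, and adherence is scored only on adequately logged days.

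**Conclusion.** The concern holds in a bounded form. The named predictors do not fit the model they serve. If followed as written, they attenuate the hypothesised paths that involve imputed variables, roughly in proportion to the missing fraction. At the planned 25 of 150, each affected path is about 17–20% low. The amplitude–symptoms–QoL indirect effect is about 18% low if outcomes are fully retrieved and up to about 35% low if amplitude, symptoms and QoL are lost together. Paths between fully observed variables are unaffected, and direct or incompletely adjusted paths can move away from zero.

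The size rests on four assumptions: the list is the whole imputation model, data are missing completely at random, amplitude is treated as observed rather than latent, and adherence→amplitude has an assumed strength. The direction for the affected hypothesised paths does not depend on the exact path sizes. This is a stated rule that gives a biased estimate, not detail left to a fuller document.

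**What to change.** Either of two changes to the missing-data paragraph is enough:

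1. Fit both SEMs by full-information maximum likelihood with auxiliary variables.
2. Keep multiple imputation, but with a model that holds every SEM variable: adherence, the three gene amplitudes at both visits, glucose tolerance, inflammation, and MADRS, YMRS and QoL.BD at all visits.

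In both cases keep the listed demographics and history as auxiliaries and add PHQ-9 and PMQ-9. State which analysis is primary and what role the analysis without imputed values has.

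The cost is one paragraph of wording. No new data, visits or participants are needed.
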